GSK Biologicals: GlaxoSmithKline Biologicals

GMT: Geometric Mean Titer

HBsAg: Hepatitis B surface antigen

HDCV: Human Diploid Cell Vaccine

Hgb: Hemoglobin

HLA: Human leukocyte antigen

hpf: High power field

HSPC: Human Subjects Protection Committee (PATH IRB)

HSRRB: Human Subjects Research Review Board (MRMC)

HURC: Human Use Research Committee (WRAIR)

IATA: International Air Transport Association

IAW: In accordance with

ICH: International Conference on Harmonization

ID: Identification

IEC: Independent Ethics Committee

IFA: Indirect fluorescent antibody

IFN-gamma: Interferon gamma

IL‑2: Interleukin 2

IM: Intramuscular; intramuscularly

IRB: Institutional Review Board

ITT: Intention-to-treat

IU: International units

IU/l: International units per liter

IV: Intravenous; intravenously

kDa: kiloDalton

KEMRI: Kenya Medical Research Institute

KSDH: Kombewa Sub-District Hospital

Ksh: Kenya shillings

LDH: Lactate dehydrogenase

LMM: Local Medical Monitor

MBF: Malaria blood film

MHRA: Medicines and Healthcare products Regulatory Agency (UK)

ml: Milliliter

mmol/l: Millimoles per liter

MPL: Monophosphoryl Lipid A

MSP-1: Merozoite surface protein 1

MVI: Malaria Vaccine Initiative

NANP: Repeat epitopes of the circumsporozoite protein

NA: Not applicable

ND: Not done

NNPGH: New Nyanza Provincial General Hospital, Kisumu, Kenya

NR: Not related

o/a On or about

OD: Optical density

ORP: Office of Research Protections, USAMRMC

PATH: Program for Appropriate Technology in Health

*P. falciparum*: *Plasmodium falciparum*

PB: Probable

PBMC: Peripheral blood mononuclear cells

PCR: Polymerase chain reaction

PCV: Packed [red blood] cell volume

PO: Administered orally

POC: Point of contact

PPD: Pharmaceutical Product Development

QA: Quality Assurance

QC: Quality Control

QS21: *Quillaja saponaria* 21 (saponin derivative)

RAP: Reporting and Analysis Plan

RCO: Registered Clinical Officer

RIA Radioimmunoassay

RNAE: Reportable non-serious adverse event

RR: Relative risk

RTS,S: A candidate pre-blood stage malaria vaccine antigen [See next 2 entries]

RTS: Fusion protein consisting of a circumsporozoite protein-based antigen and the hepatitis B surface antigen (HBsAg)

S: 226 amino acid polypeptide corresponding to the surface antigen of hepatitis B virus (adw serotype)

SAE: Serious adverse event

SB Biologicals/SB Bio: SmithKline Beecham Biologicals

SB62: An oil-in-water emulsion

SBAS2: SmithKline Beecham Adjuvant System 2

SCI: Statistics Collaborative, Inc.

SD: Study Day (Study Day 0 = 1st vaccinations)

Sf9: Insect cells derived from *Spodoptera frugiperda* (army worm)

SI: *Systemè* *International* [*d’Unité*]; International System [of

Units]

SID: Subject identification (number or card)

SOP: Standard Operating Procedure

SSC Scientific Steering Committee of KEMRI

SSP: Study Specific Procedures

SQ: Subcutaneous; subcutaneously

SU: Suspected

TBD: To be determined

TRAP: Thrombospondin-related anonymous protein

µg : Microgram

UL: Unlikely to be related

ul (or µl): Microliter

UAE: Unexpected Adverse Event

USAID: US Agency for International Development

USAMMDA: US Army Medical Materiel Development Activity

USAMRMC: US Army Medical Research and Materiel Command

USAMRU-K: US Army Medical Research Unit-Kenya

USD: United States dollars

Vacc: Vaccination

WB: Western Blot assay

WRAIR: Walter Reed Army Institute of Research, Silver Spring,

DC, USA

WRAMC: Walter Reed Army Medical Center, Washington, DC, USA

WRP: Walter Reed Project (USAMRU-K, local name)

WRP KC: WRP Kombewa Clinic

Glossary of Terms

**Blinding, Full**  Fully blind means that from Study Day 0 to 240, the only persons with access to individual study arm assignments will be (a) the two on-site Vaccine Preparation Teams consisting of the study pharmacist, pharmacist assistants, and drug manager, and (b) the statisticians preparing the randomization schedule who will not be performing statistical analysis until the study is unblinded.

**Blinding, Partial** Kenya site investigators and parents/subjects will remain blinded from Study Day 0 until full study unblinding. During the partially blinded period (from SD 240 to full unblinding), the study statisticians will be unblinded to individual and group study arm assignments so they can analyze the EFP database. (With release of the FESDR, study partners, including all investigators, will be unblinded to study results.)

**Clinician** A physician or clinical officer (physician assistant)

**Comparator** Rabies vaccine

**Drug Manager** A pharmacist, nurse, clinician, or research coordinator responsible for ensuring proper storage and accountability of test and comparator vaccines

**Eligible** In complete accord with all inclusion and exclusion criteria and, thus, qualified for enrollment into the study

**Enrolled** Eligible and having received at least one vaccine dose

**Evaluable** Eligible and having complied with all procedures defined in the protocol (see Section 12 for specific criteria)

**Local Medical** A medically qualified, host-country individual responsible

**Monitor** for actions with regard to the ethics and clinical safety of the study, especially the proper assessment of adverse events

**Parent/guardian** The biological parent or legal guardian granting informed parental consent for a child to enroll in the study

**Participant** Either a subject or a parent/guardian

**Sponsor** The study sponsor is the Office of the Surgeon General (OTSG), Department of the Army; OTSG authority devolves to the Office of Research Protections, US Army Medical Research and Materiel Command (USAMRMC-ORP); ORP in turn monitors regulatory compliance via the US Army Medical Materiel Development Activity (USAMMDA; Point of Contact: [name]) and its human subject research is authorized by its Human Subjects Research Review Board (HSRRB; Point of Contact: [name], Vice Acting Chair)

**Study Auditor** An individual responsible for auditing the work of the Study Monitor(s)

**Study Monitor** An individual responsible for assuring proper conduct of a clinical study at one or more investigational sites

**Subject**  A child enrolled in the study

**Test article**  The FMP1/AS02A candidate malaria vaccine (The WRAIR’s MSP-1antigen adjuvanted in GSK Biologicals’ AS02A)

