# STUDY DESIGN and METHODOLOGY

## Overview

- Double-blind, randomized, controlled, phase IIb (pilot efficacy) field trial of a candidate antigen/adjuvant
- One study center, with 12 outlying (satellite) field stations
- Screening will be performed no more than 45 days prior to the first inoculation
- 400 subjects will be randomized 1:1 between two arms (FMP1/AS02A and rabies vaccine)
- Immunization schedule will be 0, 1, and 2 months for both study arms
- The four-week intervals between doses may be extended for up to two additional weeks if *temporary suspension* (see Section 6.9.1) is deemed advisable because of SAEs or other concerns
- All subjects will be randomized on the day of first vaccination
- Route of inoculation will be by IM injection into the left anterolateral thigh muscle (unless compelling reason for an alternate injection site is evident)
- Study duration will be approximately about 14 months per subject
- Seven-day follow-up period for solicited adverse events (five visits: vaccination day plus post-vaccination days 1, 2, 3, and 6)
- Thirty day follow-up period for unsolicited adverse events (vaccination day plus 29 subsequent days)
- Follow-up of serious adverse events (SAEs) for study duration
- Efficacy Follow-up Period (EFP): Starting 14 days after the third vaccination (Study Day 71), active case detection commences with visits approximately every 28 days to the WRP Kombewa clinic and terminates after six months (o/a Study Day 240): EFP = 169 days = six (28 day) months
- The primary study analysis for all endpoints will be done on the cleaned EFP database after a data-lock-point
- Addendum Efficacy Follow-up Period (AEFP): Starting with the end of the EFP (o/a Study Day 240), active case detection commences with visits approximately every 28 days to the WRP Kombewa clinic and terminates after 10 months (o/a Study Day 364); AEFP = 125 days = four and a half (28 day) months. This portion of the trial is partially unblinded.
- The study addendum analysis for all endpoints will be done on the AEFP database after a data-lock-point
- Malaria cases will be detected by active and passive means
- Active case detection will be through scheduled, facilitated visits by participants to the Kombewa clinic and scheduled, field worker visits to participants’ homes
- Passive case detection will take place by unscheduled, self-presentation of participants to the Kombewa Clinic

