## Final and Addendum Efficacy and Safety Analyses and Reports

The “Final Efficacy and Safety Data Report” (FESDR) will reflect the fully blinded period of efficacy surveillance from about SD 71 to about SD 240 (specific days differ among subjects, but all subjects will be surveilled for 169 days = six [28 day] months). This is the formal “Efficacy Follow up Period” (EFP). The FESDR will address the study objectives (Section 5), endpoints (Section 12.1), and test null hypothesis (Section 5.4) for the effect of the test article during the EFP (six months). A cleaned EFP database will be submitted to SCI; SCI will query the data, lock the database, and ultimately distribute the FESDR to the DSMB and all study partners as soon as it is available. No interim analysis will be performed. .

After the completion of the EFP, the study will continue in a partially unblinded manner (for efficacy, immunogenicity, and SAEs) for another 4 months. This period of additional efficacy surveillance lasts from about SD 240 to about SD 364. At the end of this 4 ½ month partially unblinded phase, SCI will receive a cleaned database. Information from this database will be appended to the FESDR.

The FESDR will be conducted on final, cleaned data. It will include sections on intention-to-treat (ITT) analyses and will reflect safety and efficacy surveillance data from SD 0 to SD 240 ~~71).~~ The AEFP data will be analyzed on final, cleaned data and appended to the FESDR.

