### Breaking the Study Blind

A subject's study randomization code may be unblinded only for safety purposes. Such exceptional procedures should be discussed by the sponsor, the PI, the LMM, and the DSMB. If deemed necessary for reasons such as safety, the LMM or the Drug Manager (in Kenya) or SCI (in the US) will unblind a specific subject without revealing (unless clinically indicated) the study blind to the investigators. Any opening of these coded envelopes will be well documented.

The PI and Kenya field team members will remain blinded to all individual study data until the completion of the study (SD 364; for details, see Section 6.10 and Glossary). The study will remain fully blinded until the distribution of the FESDR; thereafter, it will continue in a partially unblinded fashion for the remainder of the study duration. Full unblinding will occur after study day 364, upon release of the appended study information. If a study code becomes known to the PI prior to the study’s partial unblinding (upon distribution of the FESDR), the PI must notify the sponsor immediately and document the reasons for unblinding in the study record.

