# DATA MANAGEMENT and ANALYSIS

Data entry will be performed on site at the WRP Kombewa Clinic. The CRCs will remove duplicate CRF pages periodically after review and/or approval of the study monitors and will submit to the data entry center. Statistics Collaborative, Inc., Washington, DC, USA will perform data analysis and reporting.

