### Secondary Endpoints

Because this is a Phase IIb trial, it has many secondary endpoints. Their purpose is to gain insight into the efficacy of the vaccine and to help define a primary endpoint for a confirmatory Phase III trial. They are not intended for use to make formal claims about the vaccine.

Measurements of efficacy during the EFP:

- Times to clinical episode of *P. falciparum* malaria meeting the various secondary case definitions shown in Exhibit 8
- Time to presence of asexual stage *P. falciparum* parasites during the six-month efficacy follow-up period
- Time to parasite density  50,000 asexual stage *P. falciparum* parasites per microliter of blood during the six-month efficacy follow-up period
- Number of clinical episodes of malaria, per subject, meeting the primary case definition
- Presence of MSP-1 3D7 parasites in clinical cases of malaria meeting the primary case definition
- Presence of MSP-1 3D7 parasites at a given cross-section survey time
- Time to anemia defined as Hgb < 8.0 g/dl, whether by active or passive case detection
- Proportion of subjects with anemia (Hgb < 8.0 g/dl)

Safety during the EFP:

- Occurrences of solicited AEs during a seven‑day follow-up period (vaccination day and six subsequent days) after each vaccination (five visits: vaccination day and days 1, 2, 3, and 6)
- Occurrences of unsolicited AEs during a 30-day follow-up period after each vaccination (vaccination day and 29 subsequent days)
- Occurrences of SAEs between the first vaccination and the end of the EFP

Immunogenicity during the EFP:

- Geometric means of MSP-1 Ab titers at Visits 2, 7, 12, 17, 20, and 23 (o/a Study Days 0, 29, 57, 85, 171, and 256)

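### The protocol gives conflicting times for unblinding the statisticians, does not tie code release to database lock, and uses SD 240 although each child's 169-day efficacy period ends on a different day

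*Protocol*

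**What the plan says.** **When the codes open.** The Glossary defines full blinding as running from SD 0 to SD 240. Of what follows it says: "During the partially blinded period (from SD 240 to full unblinding), the study statisticians will be unblinded to individual and group study arm assignments". The stated purpose is analysis of the EFP database. Section 9.5.2 (Breaking the Study Blind) says: "The study will remain fully blinded until the distribution of the FESDR". It also places the partial unblinding at that distribution.

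**Who handles the data.** Section 6.10: "A cleaned EFP database will be submitted to SCI; SCI will query the data, lock the database, and ultimately distribute the FESDR". Section 12: "Statistics Collaborative, Inc., Washington, DC, USA will perform data analysis and reporting".

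**What the lock controls.** Section 6.1: "The primary study analysis for all endpoints will be done on the cleaned EFP database after a data-lock-point". This makes the analysis wait for the lock. No sentence makes code release wait for it. Section 6.1 puts the analysis at about month 10.

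**What is left to judgement.** The primary analysis uses the ATP cohort (Section 12.4.2). That cohort excludes children with protocol violations deemed important (Section 12.2.2), without saying who decides or when. Section 12.4.2 also adjusts time at risk for antimalarial use and temporary absence, without giving the rule.

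**When the EFP ends.** Section 6.10 says that specific days differ by child but that "all subjects will be surveilled for 169 days". Section 7.1.6 ends the EFP at SD 240, and Section 12.4.2 censors there. Section 12.1.2 lists, as immunogenicity during the EFP, "Geometric means of MSP-1 Ab titers at Visits 2, 7, 12, 17, 20, and 23". Visit 23 is scheduled at about SD 256.

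**The concern.** The trigger for releasing individual codes is a study day, although the event that should govern it is a locked database. The organisation that reports the trial also raises queries and locks the data. If SD 240 is applied as written, people who know the arms could be present while several inputs to the primary result are still open: outstanding queries, which violations remove a child from the ATP cohort, and how much time at risk is subtracted.

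Success is a two-sided log-rank p below 0.05 (Section 5.4), so a handful of discretionary exclusions could matter near the boundary. The two blinding rules cannot both be followed, and an analysis plan cannot decide which protocol rule governs. The mismatch between SD 240 and 169 days per child adds another choice that should not be made with codes open.

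**Working it through.** **1. The blinding rules side by side**

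- Glossary: full blinding ends at SD 240, and the statisticians then hold individual codes.
- Section 6.10: a partially unblinded phase follows the EFP. SCI receives the cleaned EFP database, queries it, locks it and reports.
- Section 9.5.2: fully blinded until the FESDR is distributed.
- Section 12.4: the RAP is to be prepared before all subjects reach SD 240 and partial unblinding occurs.

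The FESDR tests the between-arm null hypothesis (Section 6.10), so someone must hold the codes before it is distributed. Section 9.5.2 therefore cannot be followed literally. The Glossary can be followed, but then nothing prevents codes being open before the lock.

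**2. Length of the exposed interval**

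SD 240 to the end of month 10 depends on the month used:

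- 28-day months, as used for the EFP: 10 × 28 − 240 = 40 days.
- 30-day months, as in Exhibit 5: 10 × 30 − 240 = 60 days.

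This is an upper bound. It assumes code release exactly on SD 240 and cleaning throughout.

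**3. Each child's EFP end**

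Inputs are the dose 3 date, 14 days to EFP start, and 169 days of follow-up. The nominal case is 57 + 14 + 169 = SD 240, which reproduces the protocol's figure.

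- Visit schedule (Section 7.2, dose 3 on day 57, read as plus or minus 9): dose 3 on SD 48 to 66, EFP start SD 62 to 80, EFP end SD 231 to 249.
- Exhibit 6 intervals stacked (28 ± 9, twice): dose 3 on SD 19 + 19 = 38 to 37 + 37 = 74, EFP start SD 52 to 88, EFP end SD 221 to 257.

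Under the visit schedule, censoring at SD 240 gives between 240 − 80 = 160 and 240 − 62 = 178 days, against 169. At the Section 12.3 control hazard of 0.1155 per month, nine days carry an event risk of about 1 − exp(−0.1155 × 9/30.4) = 3.4% for a control child still at risk at the edge of the window. This should affect both arms alike.

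Section 7.2 lets one study day span up to 25 calendar days across children, and the Glossary does not say whose SD 240 counts. If it is the first child's, codes could open while others are still under primary-endpoint surveillance.

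**4. Visit 23**

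The visit is scheduled 256 − 240 = 16 days after the nominal EFP end. The early edge of its window, 256 − 14 = SD 242, is also past SD 240.

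**5. How sensitive the primary test is (hypothetical)**

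The planning figure reproduces first. After 20% dropout there are 160 per arm. The risks are 0.500 and 1 − 0.5^0.62 = 0.349, so events are 160 × 0.849 = 135.9. Power is Φ(√135.9/2 × |ln 0.62| − 1.96) = 79.6%, against the stated rough 80%.

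Now suppose 80/160 control and 64/160 vaccine cases:

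- HR = ln(0.60)/ln(0.50) = 0.74; z = |ln 0.737|/√(1/80 + 1/64) = 1.82; p = 0.069.
- With three vaccine-arm cases excluded (61/157): HR 0.71, z = 2.02, p = 0.044.

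In a log-rank simulation with no vaccine effect (160 per arm, 4,000 runs), the chance of a significant result favouring the vaccine was 2.9%. It rose to 4.3%, 5.6% or 7.8% when 3, 5 or 8 vaccine-arm cases were dropped. Nothing in the protocol suggests that such one-sided exclusions would occur.

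**The case against.** The strongest reply is that SD 240 only names a period. The Glossary releases codes so that the EFP database can be analysed, and Section 6.1 places that analysis after lock, so release at lock is a natural reading. No passage says codes are handed over while queries are open. This is fair, but the protocol does not state the sequence, and the conflict with Section 9.5.2 remains.

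The safeguards are real. The RAP is due before partial unblinding (Section 12.4), and the DSMB may review and approve it (Section 13.3.2). It is not shown here and may define ATP violations. The database reaches SCI already cleaned. Site investigators stay blinded. An ITT analysis checks robustness.

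A reader might go further and infer three things that the documents do not support:

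- **That the unblinded statisticians must judge ATP violations.** The protocol assigns that judgement to nobody. It is also an inference that every SCI person who queries or locks data holds the codes.
- **That 80 of 400 children need an ATP decision.** These are the 20% assumed to drop out during immunization. They fail the three-dose rule, which needs no judgement, and the 160 per arm above already excludes them.
- **That unblinded staff would correct fever or density values.** Case report form changes are made by authorised individuals, and errors found in later in-house review need an investigator's approval (Appendix E). The Kenya site investigators remain blinded.

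On the EFP end, Section 6.10 already gives the per-child rule and calls SD 240 approximate. Only Sections 7.1.6 and 12.4.2 need to follow it.

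**Conclusion.** The point holds as a contradiction and a missing safeguard. The Glossary and Section 9.5.2 set incompatible times for unblinding, and code release is not tied to lock. The ATP primary analysis also contains decisions with no named decision maker. Bias is possible and is not demonstrated. The 40 to 60 days and the p-value shift rest on the assumptions stated above and are not predictions.

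The EFP-end mismatch is certain from the text. Its size is about SD 231 to 249 under the visit windows, or SD 221 to 257 if the Exhibit 6 intervals are stacked. Its direct effect on the arm comparison should be small because it does not depend on arm. The Visit 23 label is minor: it concerns a descriptive secondary measure that is also listed as tertiary.

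**What to change.** 1. In the Glossary, replace SD 240 as the trigger. Codes go to the analysing statisticians only after three dated steps: RAP approved, EFP database locked, and ATP membership and time-at-risk adjustments signed off blind. Name who decides ATP membership.
2. Align Sections 6.10 and 9.5.2 with that rule. Section 9.5.2 should say who stays blinded until the FESDR is distributed, and except the analysing statisticians after lock.
3. In Sections 7.1.6 and 12.4.2, define EFP end and censoring as each child's EFP start plus 169 days, as Section 6.10 already implies.
4. Relabel the Visit 23 (SD 256) titer in Section 12.1.2, and in the matching Summary entry, as falling after the EFP. Section 12.1.3 already carries it.

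The cost is wording in those sections, and code release moves by the weeks needed to lock. Sample size, power and alpha are unchanged.

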- At scheduled clinic visits, blood samples from all subjects will be taken to determine parasite density and hemoglobin levels. At home visits, only subjects with fever or history of fever within 24 hours (or other illness) will be transported to the clinic and sampled for detection of parasite densities and hemoglobin.
- The primary study analysis conducted at about month 10 (on the EFP data through SD 240) will be considered a “final” analysis; the study will continue an additional 4 months in a partially unblinded fashion (the AEFP data).

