### Analysis of Safety

The overall percentage of subjects with at least one local AE (solicited and unsolicited) and the percentage with at least one general AE (solicited and unsolicited) during the seven-day follow-up period after vaccination will be tabulated. The incidence, intensity, and relationship of individual solicited symptoms over a seven-day period of follow‑up (day of vaccination, plus days 1, 2, 3, and 6) will be calculated for each study arm.

The number of subjects with at least one report of unsolicited AE reported up to 30 days after vaccination will be tabulated by study arm. The intensity and relationship to vaccination of the unsolicited symptoms reported will also be assessed.

SAEs are expected to be rare, but where observed will be described. Analysis of safety during the 12-month follow-up period (ten months after dose 3) will consist of comparison of incidence of SAEs as well as of changes in mean hemoglobin levels.

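### Site investigators may learn by-arm results partway through the Addendum Efficacy Follow-up Period (AEFP), and the partial-blinding entry contradicts itself on the point

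*Protocol*

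**What the plan says.** The glossary entry on partial blinding makes two statements. The first is "Kenya site investigators and parents/subjects will remain blinded from Study Day 0 until full study unblinding". The second, in parentheses at the end of the entry, is "With release of the FESDR, study partners, including all investigators, will be unblinded to study results". It makes no exception for the Kenya site.

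Section 6.10 says the statistical group will lock the efficacy follow-up (EFP) database and "ultimately distribute the FESDR to the DSMB and all study partners as soon as it is available". Section 6.9.4 lists the PI among the study partners. On timing, Section 6.1 refers to "The primary study analysis conducted at about month 10 (on the EFP data through SD 240" as a final analysis, with follow-up continuing after it.

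Section 9.5.2 uses a narrower idea of what stays hidden at the site: "The PI and Kenya field team members will remain blinded to all individual study data until the completion of the study". It keeps the study fully blinded until the FESDR is distributed; "thereafter, it will continue in a partially unblinded fashion for the remainder of the study duration". Finally, "Full unblinding will occur after study day 364, upon release of the appended study information".

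**The concern.** The first glossary sentence promises site blinding without qualification, and the last one gives the same people the trial results before full unblinding. A site reader cannot tell from the entry whether by-arm results may be seen during the AEFP.

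The site still exercises judgement in that period. Under Section 6.3.1 the PI, associate investigators and clinical officers do the clinical evaluations. Section 7.3.2 makes a blood film depend partly on whether the clinician suspects malaria. Section 10.3 makes SAE causality a matter of opinion. After SD 240 that opinion decides between 24-hour and slower reporting (Sections 7.1.6 and 10.5.2). An assessor who knows whether the vaccine worked, and how its safety compared, may sample or attribute differently.

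The exposed analyses are the AEFP endpoints, the combined EFP and AEFP endpoints (Section 12.1.3), the 12-month SAE comparison (Section 12.4.4), and the Cox models with time-dependent covariates for follow-up period (Section 12.4.2). The last are the most exposed, because a change in assessor knowledge partway through follow-up would be confounded with a change in efficacy over time.

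**Working it through.** The protocol states no figure for this point, so the check compares the passages and then does date arithmetic.

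**1. Does the site receive by-arm results?** The glossary says all investigators do. Section 6.10 names all study partners, and Section 6.9.4 counts the PI as one. The FESDR covers the study objectives, the endpoints and the test of the null hypothesis for the EFP (Section 6.10), and Section 12.4 plans these by arm. So yes, at group level.

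**2. Does the site receive individual assignments?** No passage says so. Section 9.5.2 keeps individual data from the PI and field team to SD 364. The exceptions are the unblinded vaccine preparation team and code breaks for safety.

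**3. Is release meant to fall inside the AEFP?** Yes. Section 9.5.2 has the study carry on after FESDR distribution, with full unblinding only after SD 364. A smaller mismatch is that the glossary starts the partial period at SD 240, while Section 9.5.2 starts it at FESDR distribution.

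**4. How long is the overlap?** The AEFP runs from about SD 240 to about SD 364, and 364 − 240 = 124 days. Scheduled AEFP clinic visits fall at about SD 256, 284, 310, 340 and 364 (Section 7.2). The days left after release are 364 minus the release day. Section 6.1 does not say how its months are counted, so the table varies this and assumes release at the time of the analysis.

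| Reading of month 10 | Study day | AEFP days left | Share of 124 | Clinic visits left (of 5) |
|---|---|---|---|---|
| 10 months from screening (304 − 45) | 259 | 364 − 259 = 105 | 85% | 4 |
| 10 × 28 days | 280 | 364 − 280 = 84 | 68% | 4 |
| 10 × 30 days | 300 | 364 − 300 = 64 | 52% | 3 |
| 10 × 30.4 days | 304 | 364 − 304 = 60 | 48% | 3 |

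Exhibit 5 places month 10 at SD 271 to 300, which leaves 93 to 64 days (75% to 52%), inside the same range.

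These are upper figures, because Section 6.1 dates the analysis and not the release. Any lag between the two shortens the overlap. Release after SD 364 makes it nil.

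**5. Is the primary endpoint touched?** No. Its window is SD 71 to SD 240, which closes before any release.

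**The case against.** The strongest reply is that this is a disclosed design choice. Sections 6.1 and 6.10 and Exhibit 5 call the AEFP partially unblinded, and Exhibit 5 labels only the EFP as fully double-blinded. A reader might infer that the glossary promises a double-blind addendum period and then breaks the promise. It does not: the entry defines partial blinding. The passages can also be read together if blinding means not knowing which child received which vaccine, as in Section 9.5.1. That reply stands for individual masking. It does not cure the unqualified first sentence of the entry, and it does not remove the effect of known group results on assessors.

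A reader might also infer that the FESDR would reveal individual allocations, and the documents do not support that either.

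- **Swelling at the injection site.** The by-arm swelling counts from Mal-031 are already printed in Exhibit 4b, and staff look for swelling after every dose. Any guessing on that basis is possible from the first dose and is mostly not caused by the FESDR. Exhibit 4b also labels its denominators as doses while its percentages fit children, so it is a poor basis for a probability.
- **Rare SAEs.** Section 12.4.4 says only "SAEs are expected to be rare, but where observed will be described". It does not specify by-arm narratives from which a child could be recognised.

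The scope for bias is limited too. A case needs a measured axillary temperature and a parasite density (Exhibit 8). Every child is sampled at scheduled clinic visits whether ill or not, and field workers must send any child with fever or recent fever to the clinic. Group results without allocation give little means of treating the arms differently. The AEFP objectives are tertiary (Section 5.3). All this lowers the weight of the point, but the discretion over unscheduled films and SAE causality remains.

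Lastly, withholding results from the PI affects safety communication, because the PI must pass new safety information to the IRBs and the DSMB (Sections 13.1.1 and 13.3.2). That objection is sound, and the fix has to provide for it.

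**Conclusion.** The point holds as a self-contradictory blinding rule with a modest, avoidable risk of ascertainment and causality bias. Site assessors may know by-arm efficacy and safety results for up to roughly half to 85% of the AEFP. This assumes that the FESDR is released when the month-10 analysis is done and that it reaches the investigators who evaluate children.

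The size of any resulting bias cannot be derived from the document. The analyses weakened are the tertiary AEFP and combined endpoints, especially the test of whether efficacy changes with time, and SAE causality in the AEFP. Individual masking is formally kept. This is a cheap improvement and not a threat to the trial's main conclusion.

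**What to change.** Amend the glossary entry and Sections 6.10 and 9.5.2 so that they state one rule. By-arm FESDR results go to the DSMB and to off-site partners. Kenya site staff who assess malaria endpoints or SAE causality receive no by-arm results until the AEFP database is locked. Safety information needed to protect subjects reaches the site through the DSMB and the Local Medical Monitor. Use the same start date for the partial period in the glossary and in Section 9.5.2.

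The cost is a change of wording, a defined safety-communication route, and a wait of a few months longer for site investigators. Off-site partners can still take development decisions on time.

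If the sponsor prefers to keep the release, the glossary should say that the site is blinded to individual assignments only. The AEFP results should then be reported as collected by assessors who knew the group results, with the actual release date given.
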